## Abstract

**Background:**

The ‘predictD algorithm’ provides an estimate of the level and profile of risk of the onset of major depression in primary care attendees. This gives us the opportunity to develop interventions to prevent depression in a personalized way. We aim to evaluate the effectiveness, cost-effectiveness and cost-utility of a new intervention, personalized and implemented by family physicians (FPs), to prevent the onset of episodes of major depression.

**Methods/Design:**

This is a multicenter randomized controlled trial (RCT), with cluster assignment by health center and two parallel arms. Two interventions will be applied by FPs, usual care versus the new intervention predictD-CCRT. The latter has four components: a training workshop for FPs; communicating the level and profile of risk of depression; building up a tailored bio-psycho-family-social intervention by FPs to prevent depression; offering a booklet to prevent depression; and activating and empowering patients. We will recruit a systematic random sample of 3286 non-depressed adult patients (1643 in each trial arm), nested in 140 FPs and 70 health centers from 7 Spanish cities. All patients will be evaluated at baseline, 6, 12 and 18 months. The level and profile of risk of depression will be communicated to patients by the FPs in the intervention practices at baseline, 6 and 12 months. Our primary outcome will be the cumulative incidence of major depression (measured by *CIDI* each 6 months) over 18 months of follow-up. Secondary outcomes will be health-related quality of life (*SF-12* and *EuroQol*), and measurements of cost-effectiveness and cost-utility. The inferences will be made at patient level. We shall undertake an intention-to-treat effectiveness analysis and will handle missing data using multiple imputations. We will perform multi-level logistic regressions and will adjust for the probability of the onset of major depression at 12 months measured at baseline as well as for unbalanced variables if appropriate. The economic evaluation will be approached from two perspectives, societal and health system.

**Discussion:**

To our knowledge, this will be the first RCT of universal primary prevention for depression in adults and the first to test a personalized intervention implemented by FPs. We discuss possible biases as well as other limitations.

**Trial registration:**

ClinicalTrials.gov identifier: NCT01151982

## Background

### Depression as a public health problem

In the European community, major depression is the most common single mental disorder, with a 12 month prevalence of 4% [1], reaching 7% in USA [2]; and in European primary care attendees increasing to 13.9% in woman and 8.5% in men [3], or 14% in Spain [4]. A systematic review of 24 cost-of-illness studies of depression has reported that depression has substantial economic consequences for society [5]. For example, in 2004 the total annual cost of depression in Europe was estimated to be €118 billion, or €253 per inhabitant [6]. Major depression is projected to rank as the greatest contributor to illness burden by 2030 in high-income countries [7] due to its high prevalence, high impact on functioning, and early age of onset [8]. Most suicides are committed by people with depression [9], and the mortality rate of depressed patients exceeds 1.65 times that of the general population [10]. Despite effective treatments for depression, curative interventions can only reduce the disease burden of depression by 20%, because not all cases are recognized as such, and when recognized not all will receive appropriate treatment or adhere to the given treatment [11]. From a public health point of view, besides improving the whole process of depression care [12], we need comprehensive approaches to depression prevention [13].

### Risk strategies and primary prevention of depression

Primary prevention aims to reduce the incidence of new episodes of depression. When preventive measures are applied to the general population, regardless of their risk factors, primary prevention is called “*universal prevention*”. All randomized controlled trials (RCT) of universal prevention of depression have been conducted in children and/or adolescentes [14,15]. If primary prevention strategies are applied to people who have risk factors for depression, then it is called “*selective prevention*”. Here RCT have been undertaken in children and adolescents [16,17], elderly people [18,19], and in adults with specific risks for depression: stroke [20], postpartum [21-23], cancer [24], diabetes [25], macular degeneration [26], patients with complex medically illnesses [27], caregivers of relatives with dementia [28], or social risk patients [29], among others. A particular group of people at risk of depression are those with depressive symptoms, which do not meet DSM-IV diagnostic criteria for major depression. Primary prevention in this group of 105 people who are "subclinically depressed" is referred to “indicated prevention” [30-32].

### The ‘predictD’ algorithm

In recent years, our research group has developed and validated a risk algorithm (“the predictD algorithm”) to predict the onset of episodes of major depression in primary care attendees, in Europe [33] and Spain [34]. The Spanish algorithm obtained good calibration and discriminative validation [C-index = 0.82 (0.79-0.84)]. From 39 known risk factors of depression, 12 were included in the Spanish prediction model: six were patient characteristics or past events (sex, age, sex*age interaction, education, childhood physical abuse, and lifetime depression) and six were current status (SF-12 physical score, SF-12 mental score, dissatisfaction with unpaid work, number of serious problems in very close persons, dissatisfaction with living together at home, and taking medication for stress, anxiety or depression). The calculator of the likelihood of becoming depressed at 12 months is accessible at http://www.rediapp.org/predict.php. The "predictD algorithm" provides, in addition to the quantification of the overall risk of depression, knowledge of those risk factors influencing a given patient and that could guide a possible preventive intervention. This could allow us, as in cardiovascular disease, to develop interventions tailored in both intensity (level of risk) and specificity (profile of risk). This type of primary prevention might be called “*personalized prevention*” [35,36].

### Effectiveness of primary prevention in depression

There are at least 5 systematic reviews or meta-analyses [37-41] of effectiveness of primary prevention in depression in children and/or adolescents. A systematic review on Australian school-based prevention for anxiety and depression [37] included 24 RCT of 9 intervention programs (Friends, moodGYM, Aussie Optimism, etc.). Six were universal interventions, two indicated programs and one was a treatment program. Most were associated with short-term improvements or symptom reduction at follow-up. A meta-analysis (13–4 RCT) [38] of school-based cognitive-behavior interventions to prevent depression (all interventions were delivered at the group level) found that they were effective for reducing depressive symptoms at 1 and 3 months (with statistical significance), but at 6 and 12 months the differences were not significant. A meta-regression of other meta-analyses [39] (47 RCT and 32 prevention programs) found larger effects for programs targeting high-risk individuals, samples with more females, samples with older adolescents, programs with a shorter duration and with homework assignments, and programs delivered by mental health professional interventionists versus teachers. Another systematic review [40] (42 RCT, relating to 28 individual school-based programs) also found that indicated programs were most effective, and teacher program leaders less effective. The most recent Cochrane meta-analysis [41] (15–10 RCT) concluded that the risk of having a depressive disorder post-intervention was reduced at 3, 9 and 12 months; although there was significant heterogeneity. The persistence of the findings suggests that this is real and not a placebo effect.

A recent meta-analysis (20 RCT) [42] focusing on prevention of postpartum depression, reported a Relative Risk of 0.68 (95% CI: 0.66-0.93). Promising interventions included the provision of intensive, professionally-based postpartum home visits, telephone-based peer support, and interpersonal psychotherapy. A meta-analysis [43] of psychosocial preventive interventions to reduce depressive symptoms in low socio-economic-status women (14 RCT) found an overall effect size of 0.31(95% CI:0.17-0.45). A meta-analysis (4 RCT) [20] identified a significant effect (Odds Ratio:0.64; 95% CI:0.42-0.98) of psychotherapy for preventing depression after stroke, but there is no evidence of efficacy of antidepressants in preventing depression (10 pharmaceuticals RCT) [20].

On the other hand, there are 4 meta-analyses [44-47] that mixed different types of populations. The first [44] evaluated 7 RCT of psychological treatments for patients with subthreshold depression. The relative risk of developing a major depressive disorder in subjects who received the intervention was 0.70 (95% CI: 0.47-1.03). The second [45], combining 6 RCT that used cognitive-behavioral training called “coping with depression” to prevent depression, found an Incidence Rate Ratio (IRR) of 0.62 (95% CI: 0.43-0.91). The third [46] (19 RCT and 21 comparisons) included different types of prevention (universal:2, selective:11 and indicated:8), age (adolescents: 9 and adults:12), interventions (cognitive-behavioral:15, interpersonal:3 and others:3), format (groups:18 and individual:3), target group (postpartum:7, school:6 and other:8), and type of prevention (universal:2, selective:11 and indicated:8). The combined IRR was 0.78 (95% CI: 0.65-0.93). A fourth meta-analysis [47] adding 11 further RCT to the previous meta-analysis [46] reported an IRR of 0.74 (95% CI: 0.65-0.85).

### Justification

Data suggest that interventions to prevent depression are effective, although this effect seems small or moderate and there are a number of limitations: 1) a lack of evidence on longer term follow-up; 2) many RCT had samples of insufficient size to find significant differences for the incidence of new depression cases; 3) data suggest that universal prevention has a lower effect than selective and indicated prevention, although this affirmation is only applicable for school-based interventions, since no RCT has applied universal prevention in adults; and 4) there are no conclusive data on the superiority of any one intervention. On the other hand, cost-effectiveness studies on prevention of depression are scarce [48-50], so further investigations are needed to decide on the general implementation of primary prevention programs for depression [51,52].

Most primary prevention of cardiovascular diseases is performed in primary care and the community, while specialists (cardiologists, endocrinologists, nutritionists, etc.) play a role more focused on complicated and serious cases. This is also the case in depression. The target for primary prevention of depression is the healthy person and thus it is reasonable that primary prevention of depression is carried out in primary care and the community. However, few RCT of primary prevention of depression are conducted in primary care [28,29,32], and all the interventions were implemented by specialists in mental health (therapists, psychologists, psychiatric nurses, etc.).

We aim to conduct a cluster randomized trial in primary care with a new intervention to prevent the onset of major depression, based on the level and profile of risk of depression (personalized prevention), involving adult patients at low, moderate and high risk as measured by a risk algorithm (universal prevention) and implemented by family physicians (FPs). We will recruit a sample of non- depressed primary care patients that is large enough to detect a significant reduction in the incidence of new episodes of depression over 18 months. Our main outcome will be the effectiveness of this new intervention, but we will also assess its cost-effectiveness and cost-utility.

## Objectives

The main objective is to measure the effectiveness of a new intervention for primary prevention of major depression based on the level and profile of risk of primary care attendees. Among the secondary objectives are to evaluate the cost-effectiveness and cost-utility of the intervention versus usual care.

## Methods/design

### Design

A multicenter randomized controlled trial, with cluster assignment by health center and two parallel arms. Two interventions will be applied: usual care in the control group and a new intervention for primary prevention of major depression based on the level and risk profile of patients. These interventions will be applied by the FPs. The main outcome is the cumulative incidence of major depression during the follow-up, with evaluations at baseline, 6, 12 and 18 months. Inferences will be made at the patient level.

The predictD-CCRT study is in compliance with the Helsinki Declaration. The predictD-CCRT study has been approved by the relevant ethics committees in each participating Spanish city: Ethics Committee on Human Research of the University of Granada, Ethics and Research Committee of Primary Health District of Malaga, Ethics Committee for Clinical Research of Sant Joan de Deu Foundation (Barcelona) (PIC CEIC-62-09), Ethics Committee for Clinical Research of Aragon (CEICA) (CP06/05/2009), Ethics Committee for Health Research of the Jaen Hospital, Ethics Committee for Clinical Research of Euskadi (CEIC-E) (03/2009), Ethics Committee for Clinical Research of the Rio Hortega Hospital of Valladolid (04/2009).

### Setting

Health Centers in seven Spanish cities will participate: Malaga, Jaen and Granada in southern Spain; Valladolid in western Spain; Saragossa and Bilbao in northern Spain; and Barcelona in eastern Spain. Each health center covers a population of 15,000 to 30,000 inhabitants from a geographically defined area. The FPs in each health center work as a group, with extensive primary care teams. The Spanish National Health Service provides free medical cover to over 95% of the population. Patients can visit their doctors as often as they want without having to pay for it, even when they do so for preventive reasons. Each patient is assigned to only one FP, who has gatekeeper functions.

### Sample selection of participants and exclusion criteria

#### Health centers

From a possible total of 220 health centers in the 7 participating cities, those that do not have electronic clinical charts or have had them for less than 2 years or plan to change them in the next 18 months will be excluded. All others will be invited to participate. From those centers that agree to participate, a random sample of 10 health centers per city, 70 health centers in total, will be selected. These will then be randomized by an independent person from the research group at the coordinating center of the study (Malaga), using closed and opaque envelopes.

#### Family physicians

In each participating health center we will exclude those FPs who are unfamiliar with using the clinical chart or are planning to change their place of work in the next 18 months. We shall then invite all remaining FPs to participate and from those who agree, randomly select two per center (before randomization of centers) using closed and opaque envelopes selected by an independent person from the research group. This will mean 140 FPs will participate in the trial.

#### Patients

Patients belonging to the 140 FPs will be selected using a systematic random sampling, each 4–6 patients, from the FPs’ appointment lists at random starting points for each day. This will be done by an assistant researcher for each health center. The list of selected patients will be given every day to the family physician (FP) before starting to see patients. FPs will check the selected patients to see if they meet any of the following exclusion criteria: age under 18 or over 75 years; inability to understand or speak Spanish; severe mental disorder (psychosis, bipolar, personality disorder,…); cognitive impairment; terminal illness; the patient is scheduled to be out of the city more than four months during the 18 months of the follow-up; and persons (representatives) who attend the surgery on behalf of the person who has the appointment. The FPs will introduce the study to the selected not excluded patients and will request permission before contacting the assistant researcher. Patients who refuse to participate will not be replaced, prolonging the days of recruitment to achieve 26–27 patients for each FP. Those who give informed consent will undertake a research interview within two weeks with the Composite International Diagnostic Interview (CIDI) in order to detect the presence of major depression. Patients with a diagnosis of current major depression will also be excluded from the trial. The exclusion criteria for health centers, FPs and patients are shown in Table 1.

**Table 1 T1:** Exclusion criteria of the predictD-CCRT study

***Health centers***	
•	Do not have electronic clinical charts or have had them for less than 2 years
•	Plan to change their electronic clinical charts in the next 18 months
•	No consent to participate in the study
***Family Physicians***	
•	Unfamiliar with using the clinical chart
•	Planning to change their place of work in the next 18 months
•	No consent to participate in the study
***Patients***	
•	Age under 18 or over 75 years
•	Inability to understand or speak Spanish
•	Severe mental disorder (psychosis, bipolar, personality disorder…)
•	Cognitive impairment
•	Terminal illness
•	The patient is scheduled to be out of the city more than four months during the 18 months of follow-up
•	Persons (representatives) who attend the surgery on behalf of the person who has the appointment
•	Diagnosed with major depression by the CIDI*
•	No consent to participate in the study

* Composite International Diagnostic Interview.

### Randomized allocation

The randomization and allocation to the arms will be carried out according to the health center; that is, all FPs and patients from one health center will be included in the same arm. If the same health center has FPs in both the control and the intervention groups, the likelihood of the FPs in the control group becoming contaminated by the intervention group is high, since Spanish health centers generally work as a team. We aim to evaluate a new intervention for primary prevention of major depression, which in principle will be delivered at patient level by the FP; however, due to the nature of the intervention some components could be delivered at community level, so the contamination between patients in the control and intervention groups in the same health center is likely. Therefore we have decided on cluster randomization to avoid this possibility in patients and FPs.

The randomization of the 70 health centers to allocate them to the control or intervention groups will be done stratifying by city. Thus, we will have 35 health centers assigned to the control group and 35 to the intervention group, 5 and 5 respectively for each one of the seven cities participating in our study. The randomization will be undertaken centrally, from the coordinating center in Malaga, by an independent person outside the research group using closed and opaque envelopes.

### Masking

In trials that evaluate psychosocial interventions it is not possible for professionals who provide the new intervention or for patients who receive it to be blind to it [53]. However, in our trial those who assess outcomes (interviewers) will be different and independent from those who provide the intervention (FPs). Moreover, the interviewers will be not informed of the patient’s status in the control or intervention group. Those who perform statistical analyses will also be blind to the intervention and control codes.

### Sample size

The sample size was calculated assuming that the cumulative incidence of depression in the control group will be 12% [34] while the incidence in the intervention group will be 5 points below that 12%. The Type I error of the chosen contrast was 5% and the power 80%. The sample size obtained assuming a simple random sample would be 430 people in each group. As we will undertake a cluster randomization (by health center), and decided to have 35 health centers in the control group and 35 in the intervention group (48 patients in each health center), we obtained an effect design of 3.82, with the assumption that the intraclass correlation coefficient of the health center is 0.06 [34]. Thus we need a sample size of 1643 patients in each trial arm, making a global sample of 3286 patients, 140 family doctors and 70 health centers. These calculations assume that the distribution of 2 FPs per health center and 24 patients per FP will be very homogeneous (coefficients of variation of cluster sizes <0.15). We also expect to increase the sample of patients recruited by FPs from 24 to 26–27, since about 10% of potential patients will have a diagnosis of major depression on CIDI at baseline and will need to be excluded.

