If many health centers and FPs refuse to participate, we could encounter a selection bias as the FPs who choose to participate may have a different profile (psychosocial orientation, different training and work satisfaction, etc.) to those who do not. This could limit external validity [110] and, from a pragmatic standpoint, the new intervention would be less effective when applied as a general program. Similar biases could occur if a large proportion of patients refuse to participate. It is not easy to obtain information from those physicians and patients who refuse to participate, so it will be difficult to ascertain the direction of this possible selection bias. As stated above, for the analyses with complete cases we will use the inverse probability weighting [84,85] to adjust for a possible attrition bias due to participants lost during the follow-up. We will use multiple imputations to minimize attrition bias and maintain statistical power [78,111].

The results obtained will be applicable to primary care attendees and cannot necessarily be generalized to other settings such as the general population. Nevertheless, primary care is an ideal setting for prevention and attendees are generally (because of health and social problems) at greater risk of depression than the general population.

If the predictD-CCRT intervention proves effective, it will be difficult to determine which of the 5 components are active or expendable, and how each interacts with the others. We will conduct a number of secondary analyses that could provide clues to the most relevant component, but more studies (quantitative and qualitative) specifically directed toward that goal will be needed.

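### The base figure of 430 per group fits only a one-sided 5% test; sidedness is not stated, and on the usual two-sided reading power is about 71%, not 80%

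*Protocol article*

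**What the plan says.** All the inputs are in the Sample size section of the protocol article.

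- Control arm: "assuming that the cumulative incidence of depression in the control group will be 12" per cent.
- Intervention arm: "the incidence in the intervention group will be 5 points below that 12" per cent, that is 7%.
- Error rates: "The Type I error of the chosen contrast was 5% and the power 80" per cent. One- or two-sided is not stated.
- Result before clustering: "The sample size obtained assuming a simple random sample would be 430 people in each group".
- Clustering: 35 centers per arm, each contributing 48 patients. On the inflation factor the section reports: "we obtained an effect design of 3.82, with the assumption that the intraclass correlation coefficient of the health center is 0.06".
- Result after clustering: 1643 per arm and 3286 in all, repeated in the Abstract.

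The section also raises recruitment from 24 to 26–27 per family physician, and gives one reason: about 10% of potential patients are expected to be excluded for major depression on the baseline CIDI. The Regression models section describes the primary analysis as a multilevel logistic regression giving an adjusted odds ratio for group. It gives neither the sidedness of the test nor an interval level.

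**The concern.** An unqualified 5% type I error is conventionally read as two-sided, and on that reading 430 per group is too few for 80% power at 12% versus 7%. The clustered totals are simple multiples of 430, so any shortfall in the base figure passes straight into 1643 and 3286.

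The 80% is the trial's stated chance of detecting the effect it was designed for. The Justification section faults earlier trials for insufficient size and presents this one as large enough to detect a significant reduction in incidence. If true power is nearer 70%, the chance of missing a real 5-point reduction is about 29% rather than 20%, and a null result would deserve a more cautious reading than the article invites. Leaving sidedness open also leaves a choice that could be made once results are known.

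**Working it through.** **Inputs** (Sample size section): p1 = 0.12, p2 = 0.07, difference 0.05, mean p = 0.095, alpha = 0.05, power 0.80 (z = 0.8416), ICC = 0.06, 48 patients per center, 35 centers per arm.

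**1. Reproducing the plan's figure.** The formula is n = [z_a·√(2·p̄(1−p̄)) + z_b·√(p1(1−p1) + p2(1−p2))]² / (p1−p2)², with √(2 × 0.095 × 0.905) = 0.4147 and √(0.1056 + 0.0651) = 0.4132.

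- One-sided (z_a = 1.645): (1.645 × 0.4147 + 0.8416 × 0.4132)² / 0.0025 = 424.2, so 425 per group.
- Two-sided (z_a = 1.960): (1.960 × 0.4147 + 0.8416 × 0.4132)² / 0.0025 = 538.7, so 539 per group.

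**2. Could another formula explain 430?**

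| Formula | One-sided 5% | Two-sided 5% |
|---|---|---|
| Standard, as above | 425 | 539 |
| Unpooled variance | 422 | 536 |
| Pooled variance only | 425 | 540 |
| Arcsine | 418 | 531 |
| Log odds ratio | 435 | 552 |
| Log relative risk | 439 | 557 |
| Standard with continuity correction | 464 | 578 |

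Without continuity correction, every one-sided result lies within 3% of 430. The smallest two-sided result, 531, is 23% above it (531/430 = 1.23). Rounding or choice of formula does not bridge that gap.

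**3. The clustering step.** Design effect = 1 + (48 − 1) × 0.06 = 3.82, and 430 × 3.82 = 1642.6, so 1643. Both are right. The two-sided equivalent is 539 × 3.82 = 2059 per arm, or 4118 in all: about 43 centers per arm at 48 patients each (2059/48 = 42.9), against the 35 planned.

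**4. Power at the planned size.** 1643/3.82 gives an effective 430 per arm. Power = Φ[(0.05 − z_a·SE0)/SE1], with SE0 = 0.4147/√430 = 0.01200 × 5/3 = 0.0200 and SE1 = 0.4132/√430 = 0.0199.

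- One-sided: Φ(0.859) = 80.5%.
- Two-sided: Φ(0.542) = 70.6%.

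Using the mean cluster size implied by 1643 per arm (1643/35 = 46.9; design effect 3.757; effective 437) gives 71.4% two-sided. Starting from 35 × 48 = 1680 gives 71.6%. A t reference on 68 degrees of freedom gives about 70%. "About 71%" is therefore a fair summary on the normal approximation.

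**5. Detectable difference.** For 12% versus 6.5%, two-sided power is 79.6% at an effective 430 and 80.3% at 437, so about 80%.

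**6. Loss by 18 months.** The article gives no rate; 20–30% is an assumption. Starting from 1643 per arm, with no information recovered for those lost:

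- 20% lost: 37.6 per center, design effect 3.193, effective n 412, two-sided power 68.7%.
- 30% lost: 32.9 per center, design effect 2.912, effective n 395, two-sided power 66.9%.

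Starting from 1680 gives 69.0% and 67.2%. The range is 67–69% on either basis.

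**The case against.** The strongest reply is that no step is wrong as written. The section never says two-sided, the trial's aim is directional, and under a one-sided 5% test the 430, the 3.82, the 1643 and the 80% all agree. A full protocol or analysis plan, not shown, may declare the sidedness. This stands to the extent that a one-sided intention cannot be excluded. It does not rescue the paragraph: the article publishes inputs and a result that agree only under a condition it leaves out, and most readers will assume the opposite.

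A second reply is that the planned model adjusts for a baseline risk score with a C-index of 0.82 and keeps city, the stratification factor. If that lowered the residual ICC from 0.06 to 0.05 or 0.045 (assumed values), two-sided power would be about 77% or 80%, with 48 patients per center. That is possible, but the calculation takes no credit for it and no residual ICC is given.

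Three stronger readings are tempting and not supported:

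- *That the trial's own intervals show a two-sided test.* The one 95% interval planned for trial data is for mean cost differences (Quantification of uncertainty). It says nothing about the primary odds ratio.
- *That attrition is ignored.* Multiple imputation and inverse probability weighting are both planned. What is absent is an allowance in the sample size, and its effect, about 2 to 4 points of power, rests on an assumed loss rate.
- *That "We will use multiple imputations to minimize attrition bias and maintain statistical power" is false and should go.* With CIDI interviews at 6, 12 and 18 months, a patient lost after a detected onset already has a known outcome, and one lost after a negative 12-month interview lacks only the last interval. Imputation can recover part of that information, so the phrase may stand.

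**Conclusion.** The point holds in this form: the stated 80% power is correct only for a one-sided 5% test that the article does not declare. On the conventional two-sided reading, the planned 1643 per arm has about 71% power for 12% versus 7%, roughly 9 points below the figure given. Two-sided 80% would need about 25% more patients per arm (2059/1643 = 1.25).

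This rests on the article's own incidences, ICC and cluster size, an unadjusted comparison of two proportions and a normal approximation. A reader might infer that the authors made an arithmetical slip or that the test is certainly two-sided. The text establishes neither. What it establishes is that the base figure and the usual meaning of a 5% error rate do not agree, and that the primary outcome's stated power depends on which was meant. The loss-to-follow-up figures are secondary and conditional on the assumed 20–30%.

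**What to change.** State in the Sample size section whether the primary test is one- or two-sided.

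- *If two-sided:* keep the planned sample and restate it. Before clustering, 12% versus 7% needs 539 per group; 1643 per arm gives about 71% power for that contrast, or about 80% for 12% versus 6.5%. Add that covariate adjustment may recover some power but is not credited.
- *If one-sided 5% was intended:* declare it before unblinding and use it for both the primary test and the interval around the odds ratio.

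In either case, add a sentence that the rise to 26–27 patients per physician covers only baseline CIDI exclusions, and that loss by 18 months lowers power further (about 67–69% two-sided if 20–30% are lost, labelled as an assumed range).

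The cost is a few sentences and, if the test is two-sided, a less favorable power figure. No extra patients are required unless the sponsor wants to keep two-sided 80% at 12% versus 7%, which would take about 2059 per arm.
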